## Abstract

**Background:**

The national Cancer Reform Strategy recommends delivering care closer to home whenever possible. Cancer drug treatment has traditionally been administered to patients in specialist hospital-based facilities. Technological developments mean that nowadays, most treatment can be delivered in the out-patient setting. Increasing demand, care quality improvements and patient choice have stimulated interest in delivering some treatment to patients in the community, however, formal evaluation of delivering cancer treatment in different community settings is lacking. This randomised trial compares delivery of cancer treatment in the hospital with delivery in two different community settings: the patient's home and general practice (GP) surgeries.

**Methods/design:**

Patients due to receive a minimum 12 week course of standard intravenous cancer treatment at two hospitals in the Anglia Cancer Network are randomised on a 1:1:1 basis to receive treatment in the hospital day unit (control arm), or their own home, or their choice of one of three neighbouring GP surgeries. Overall patient care, treatment prescribing and clinical review is undertaken according to standard local practice. All treatment is dispensed by the local hospital pharmacy and treatment is delivered by the hospital chemotherapy nurses. At four time points during the 12 week study period, information is collected from patients, nursing staff, primary and secondary care teams to address the primary end point, patient-perceived benefits (using the emotional function domain of the EORTC QLQC30 patient questionnaire), as well as secondary end points: patient satisfaction, safety and health economics.

**Discussion:**

The Outreach trial is the first randomised controlled trial conducted which compares delivery of out-patient based intravenous cancer treatment in two different community settings with standard hospital based treatment. Results of this study may better inform all key stakeholders regarding potential costs and benefits of transferring clinical services from hospital to the community.

**Trial registration number:**

ISRCTN: ISRCTN66219681

## Background

In the last 10 years since the Calman-Hine report [1], cancer patient care in the United Kingdom has been reorganised to deliver treatment within cancer centres and cancer units within cancer service networks. Patients benefit by accessing specialised staff, equipment and treatment at the centre, while local cancer units provide treatment for common conditions, but the quality of care received is systematised across large geographical areas. During these years, cancer incidence has been rising in an ageing UK population, while developments in diagnosis and therapeutics alongside increasing patient expectations mean that more patients than ever before are being referred for cancer drug treatment. Oncology specialist services have adapted to meet increasing demand by delivering most drug treatments in purpose-built day units. However, capacity pressures are potentially driving down efficiency and risking maintenance of quality standards. The UK Government White Paper, 'Our health, our care, our say' [2], promotes patient choice and transfer of services closer to people's homes. Treatment for cancer patients in their own homes is well established in the private sector, but community treatment has been less extensively explored within the National Health Service. Few formal studies have been undertaken to evaluate the services that do exist.

Most reports in the literature have concentrated on evaluating delivery of cancer treatment in the home. These suggest that home care is safe, while patients may experience reduced side effects [3-5] and compliance rates may improve [6,7]. The cost of delivering treatment at home is poorly understood: some reports suggesting the possibility of cost savings [8-10], while others report home delivery to be more expensive [6,11]. Private providers are keen to work with the health service to deliver treatment in the community, but concerns regarding clinical governance and cost-effectiveness have been raised [12,13]. With few exceptions [12], most published studies are small and out-dated.

Community treatment models other than homecare already exist in the UK and include roving chemotherapy delivery buses as well as satellite units in community settings akin to models already established in other specialities such as cardiology and diabetes, where hospital teams visit GP surgeries on a regular basis. The Department of Health has given a clear steer to encourage commissioning of care closer to home despite a lack of quality data to justify this recommendation [14]. The OUTREACH study aims to address the patient benefits and costs associated with delivering treatment in two different community settings compared with standard hospital-based treatment, in order to better inform future commissioning decisions.

## Methods/design

### Study Hypothesis

The primary hypothesis is that community-based chemotherapy (whether at home or in a GP surgery) offers patients improved quality of care compared with standard hospital-based treatment: patient perceived benefit is thus the primary end point. The study aims to compare delivery of systemic cancer therapy in three different settings: hospital day unit, patient's home and Outreach GP surgery, by means of a randomised controlled trial.

### Primary Aim

Patient perceived benefit, as measured quantitatively by the emotional function domain of the EORTC QLQ-C30 quality of life questionnaire.

### Secondary Aims

1) Other patient benefits identified using the Hospital Anxiety and Depression score, EQ-5D (EuroQol) and a specifically designed patient satisfaction questionnaire.

2) Qualitative assessment of the experience of treatment delivered in the three different locations, using semi-structured interviews of patients, their carers (where appropriate), and other health care professionals (doctors, nurses and hospital managers either directly or indirectly associated with this study).

3) Impact on costs and cost-effectiveness of treatment delivered in the three different locations. It will evaluate whether community care is cost-effective by measuring the costs and benefits to the NHS and to patients.

4) Patient safety, determined by the number of adverse and serious adverse events.

5) Compliance with treatment delivered in the different locations.

6) Assessment of reasons why patients decline to take part in the study.

### Ethical approval

The protocol has research ethics committee approval from the Cambridgeshire 2 Research Ethics Committee and site specific assessment approval for each site involved in the study.

### Trial design and randomisation (Figure 1)

**Figure 1 F1:**
[figure not shown]
**Trial design**.

This is a prospective, randomised, controlled clinical trial conducted at two neighbouring Trusts in the Anglia Cancer Network: Addenbrooke's Hospital (CUH) and West Suffolk Hospital (WSH). Patients meeting the defined eligibility criteria are invited to take part in the study prior to or during their planned cancer treatment. All patients taking part provide written informed consent. Patients are randomised on a 1:1:1 basis to one of 3 arms: treatment delivered in the hospital out-patient and day unit environment (control arm A), treatment delivered at home (arm B) or treatment delivered in a GP surgery (arm C) using the method of minimisation with a random element to the assignment. Randomisation is performed centrally by statisticians located separately from trial recruitment and co-ordination and without knowledge of patients or their characteristics.

In the minimisation procedure the patients are stratified by centre (CUH or WSH), by treatment intent (cure, palliation in terms of disease control and life prolongation, or supportive care aimed at symptom control), ECOG performance status (PS 0, 1 or 2), gender, and prior cancer drug treatment (yes or no).

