### Patient registration and randomisation

Eligible patients are registered with and randomised by the Outreach Trial Co-ordinator, at the Cambridge Cancer Trials Centre (CCTC), CUH. Eligible patients are allocated a unique trial number and the treatment location defined. Registration and randomisation is undertaken by fax or email and the randomisation outcome information provided to the Investigator by return, within 24 hours. The Investigator is responsible for organising the patient's treatment and follow-up.

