### Recording and collection of data

Upon randomisation of an individual patient, a pack containing specifically designed data collection forms, questionnaires and diaries is provided to the Investigator. The forms allow collection of essential information required for the study at each predefined trial data collection point. The study has four mandatory and 1 optional data collection point. Mandatory data collection points are baseline (at the start of study treatment), then approximately 4 weeks, 8 weeks and 12 weeks after commencing treatment. For patients continuing treatment beyond 12 weeks, there is an optional data collection point at 24 weeks or on stopping treatment, whichever occurs sooner. The baseline, 12 week and 24 week data collection visits take place at hospital. On these occasions, study forms will be completed by the Investigator or a member of his/her team, which may include a specialist or research nurse/practitioner. Patient questionnaires and diaries are given to the patient and/or collected from the patient as appropriate at these visits.

In order to allow for different treatment schedules, the second and third data collection points may be flexible to within 1 week either side of the planned 4 and 8 week time points. For patients having treatment in hospital, on these occasions, forms are completed by the Investigator or a member of his/her team, which may include a specialist or research nurse/practitioner. Patient questionnaires are given to and collected from the patient as appropriate at these visits. For patients having treatment in the community, these study forms are completed by the community chemotherapy nurse. Patient questionnaires are given to and collected from the patient as appropriate at these visits.

Following each planned data collection point, study forms and questionnaires are returned to the Outreach Trial Coordinator, who is responsible for creating and completing the unique patient Case Report Forms (CRF).

Patients randomised to receive treatment in either community setting may be transferred at any time to continue treatment in hospital, and the date and reason for transfer will be documented. Transfer of care to the hospital constitutes a serious adverse event (SAE) and withdrawal from the trial. Patients randomised to receive treatment in hospital may not be transferred to either location in the community, since this is not standard clinical practice locally.

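### The protocol article contradicts itself on who randomises, and minimisation on five patient factors cannot be done without knowing those factors

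*Protocol article*

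**What the plan says.** The section Trial design and randomisation describes 1:1:1 allocation to hospital, home or GP surgery "using the method of minimisation with a random element to the assignment". It then says who does it: "Randomisation is performed centrally by statisticians located separately from trial recruitment and co-ordination and without knowledge of patients or their characteristics". The next paragraph lists the factors: "In the minimisation procedure the patients are stratified by centre (CUH or WSH), by treatment intent", followed by "ECOG performance status (PS 0, 1 or 2), gender, and prior cancer drug treatment (yes or no".

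The section Patient registration and randomisation names someone else: "Eligible patients are registered with and randomised by the Outreach Trial Co-ordinator, at the Cambridge Cancer Trials Centre (CCTC), CUH". It adds the route: "Registration and randomisation is undertaken by fax or email and the randomisation outcome information provided to the Investigator by return, within 24 hours". CUH is one of the two recruiting hospitals. Under Recording and collection of data, the same Co-ordinator receives forms and questionnaires and is the person "who is responsible for creating and completing the unique patient Case Report Forms (CRF".

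The article also differs on when baseline is taken. The primary end point section puts the first QLQ-C30 before randomisation, and Statistical Analysis adjusts for a pre-randomisation baseline. Recording and collection of data issues the questionnaire pack once the patient has been randomised and places baseline at the start of study treatment. Under Treatment plan, that start may be up to 28 days after randomisation.

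**The concern.** Patients and staff know the venue as soon as it is allocated, and the primary outcome is the patient's own rating of emotional function. With no masking afterwards, concealment before allocation is an important remaining protection against selective entry. A reader of the article cannot tell who receives the patient's factors, who runs the algorithm or who holds the running totals.

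If the registration section is what is followed, the separation promised in the design section is lost, and one person at a recruiting hospital both registers and allocates. Under minimisation this matters more than under simple randomisation, because the running totals and the next patient's factors together make the next arm partly predictable.

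The baseline timing belongs to the same sequence. A patient who completes the emotional function items after learning the venue may already be reacting to it, and that score is then used as a covariate.

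**Working it through.** **1. The two accounts side by side.**

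| | Trial design and randomisation | Patient registration and randomisation |
|---|---|---|
| Who randomises | Statisticians | Trial Co-ordinator |
| Relation to co-ordination | Separate from it | Is the co-ordination |
| Place | Central, apart from recruitment | Trials centre at CUH, a recruiting hospital |
| Knowledge of patient | None | Receives the registration |

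The first two rows cannot both be true as written. They would be compatible if the Co-ordinator only relayed an allocation made by the statisticians, but no sentence says so.

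**2. What minimisation needs.** There are five factors: centre (2 levels), intent (3), performance status (3), gender (2) and prior drug treatment (2). That is 2 + 3 + 3 + 2 + 2 = 12 levels and 2 × 3 × 3 × 2 × 2 = 72 possible profiles. Each assignment compares arm counts at the new patient's own five levels. Whoever or whatever makes the assignment must therefore be given those five values.

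**3. The plan's own figure.** The article gives no number on this point. The nearest is the trial size of 130 per arm, which reproduces. With SD 24, a 10-point difference, two-sided 5% and 80% power, n = 2 × (1.96 + 0.84)² × 24² / 10² ≈ 90.4, so 91 evaluable per arm, and 91 / 0.70 = 130. The concern does not affect it. It supplies N = 3 × 130 = 390 for the next step.

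**4. Illustration of predictability.** Inputs from the article: 390 patients, three arms, the five factors and a random element. Inputs assumed: centre 70/30, intent 40/50/10, performance status 45/45/10, gender 40/60, prior treatment 50/50, and the assignment probability p. Rule: for each arm, sum over the five factors the range of arm counts if the patient went there. The arm with the smallest sum is preferred (ties broken at random) and is given with probability p; the other two share 1 − p. The guesser names the preferred arm. Results are from 200 simulated trials per p. The third column is a further set of 60 trials per p, also on assumed prevalences.

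| p | Holds full tables | Holds full tables (60 trials) | Knows overall arm totals only |
|---|---|---|---|
| 0.5 | 48% | not run | 40% |
| 0.6 | 57% | not run | 44% |
| 0.7 | 66% | 67% | 47% |
| 0.8 | 74% | 75% | 51% |
| 0.9 | 83% | 84% | 54% |

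Chance is 1/3 = 33%.

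Hand check: a single preferred arm exists in about 84% of allocations. If the other 16% are treated as two-way ties, P(correct) = 0.84p + 0.16 × [0.5p + 0.25(1 − p)].
- At p = 0.5: 0.420 + 0.16 × 0.375 = 0.480.
- At p = 0.9: 0.756 + 0.16 × 0.475 = 0.832.

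Both agree with the table. The random element lowers predictability but does not remove it, so it matters who holds the tables.

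**The case against.** A reader might infer that concealment is unprotected. The article does not support that. In both accounts the Investigator sends a request off the ward and receives the arm by return; in neither does the Investigator allocate. Both operate under minimisation with a random element. This objection stands.

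A reader might also infer that patients could be steered. That merges two people. Eligibility discretion belongs to the Investigator (Eligibility section). The Co-ordinator is given none, and nothing says that the Co-ordinator holds the running totals or passes on predictions. Completing the CRFs comes after allocation and has no bearing on concealment. This also stands.

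Third, Statistical Analysis adjusts continuous outcomes for the stratifiers, including performance status, and for the baseline of the outcome. Selective entry of fitter or more anxious patients would therefore be largely captured, leaving only unmeasured differences. This mostly stands, but it relies on a baseline taken before allocation, which Recording and collection of data puts in doubt.

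Fourth, the phrase about not knowing characteristics may simply mean nothing beyond the submitted factors, and the fax or email route fits a relay through the Co-ordinator. Both are plausible intentions, but the text says neither. The unstated assignment probability is a detail that an article may leave to the full protocol, and it is not held against the plan here.

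**Conclusion.** The contradiction is real: the two sections name different randomisers, and one claims ignorance of characteristics that the chosen method requires. As written, following the registration section would remove the separation that the design section promises, in a trial that cannot be masked and has a patient-reported primary outcome.

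The conclusion goes no further than an unclear safeguard. It does not establish that concealment is absent, that anyone could predict allocations in practice, or that the treatment effect is biased; no size of bias can be derived from the article. The range of about 48% to 84% correct guesses rests on assumed factor prevalences, assumed assignment probabilities of 0.5 to 0.9, and possession of the full tables, which the article attributes to no one involved in recruitment. It shows only why the point is worth settling. The sample size is unaffected. The text should be corrected, and the correction is cheap.

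**What to change.** State one procedure in both randomisation sections:

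1. The Co-ordinator confirms eligibility and consent, irrevocably registers the patient, and sends the trial number and the five minimisation factors to the independent statisticians.
2. The statisticians alone run the minimisation, hold the running totals and return the arm.
3. The arm is released only after the baseline questionnaires are complete, as the end point sections and Statistical Analysis already require.

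In the design section, replace the words about having no knowledge of patients or characteristics with: *without identifiers and with only the minimisation factors*. In the registration section, change the Co-ordinator's role from randomising to registering and relaying.

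Align Recording and collection of data with this, so that the baseline questionnaires are issued and completed before randomisation, with the rest of the pack following allocation.

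The cost is rewording three sections, routing one message through roles that already exist, and handing out the baseline questionnaires earlier. No change to sample size or analysis model is needed.

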### Study duration

The study period is defined as being 12 weeks on a particular course of treatment. Where patients continue treatment beyond 12 weeks, those being treated at home can continue to do so. However, if they prefer to be treated in hospital they can transfer. Those patients randomised to hospital treatment cannot cross over to treatment in the community, since community-based treatment is not standard practice locally. Patients stopping treatment earlier than 12 weeks are not replaced in the study, but the reason for stopping is noted. They are included for the collection of study outcomes at 12 weeks, since analysis is on an intention-to-treat basis.

### Eligibility

Cancer patients over 18 years of age being treated at either CUH or WSH with standard infusions of under 4 hours duration and living within a 30 minute drive of either hospital will be offered entry to this study. Eligible patients must give written informed consent and be about to commence a course of treatment planned to last a minimum of 12 weeks, or have already commenced a course of treatment which is planned to continue for a minimum of 12 further weeks. The course of treatment may be aimed at cure, palliation (disease control and life prolongation) or supportive care (symptom control). Patients need to have hot and cold running water in the home, an indoor toilet and a working telephone. Patients must be ECOG performance status < 2, or if ECOG PS 2, there must be a second individual living in the home who functions as a carer.

Patients with life expectancy under 6 months or those dependent on hospital transport are excluded. Other exclusion criteria are: any patient receiving an unlicensed cancer drug treatment as part of a clinical trial where the drug is defined as an Investigational Medicinal Product unless the trial itself has received ethics and R&D approval to be conducted in designated community settings used in the Outreach trial: patients with language barriers or communication difficulties whose safety might potentially be comprised by entry into this trial: any patient where in the opinion of the Investigator entry into this trial would give cause for concern regarding patient or staff safety.

### Patient registration and randomisation

Eligible patients are registered with and randomised by the Outreach Trial Co-ordinator, at the Cambridge Cancer Trials Centre (CCTC), CUH. Eligible patients are allocated a unique trial number and the treatment location defined. Registration and randomisation is undertaken by fax or email and the randomisation outcome information provided to the Investigator by return, within 24 hours. The Investigator is responsible for organising the patient's treatment and follow-up.

### Study interventions

The Investigator has primary responsibility for the welfare of the patient for the duration of the study, whether receiving treatment in hospital, at home or in the GP surgery. Patient treatment is governed by a single set of standard operating procedures in use at CUH, WSH (and the GP surgeries involved in this study.

The Investigator is responsible for prescribing all treatment for trial patients, but can delegate this task to a member of his or her junior staff, as is standard clinical practice.

The treatment study period for this trial is 12 weeks, since most treatments are expected to be prescribed for at least this period of time. All planned treatment for a study patient will be delivered in the location to which the patient is randomised. Treatment of patients within the community may be aborted and transferred to hospital in the event of significant problematic drug-related toxicities, occurrence of a serious adverse event (SAE), on request by the patient, or following discussion between the community chemotherapy nurse and the Investigator who may feel it is in the patient's best interest to do so. The Investigator will review the patient in clinic prior to study entry and on completion of the study (whether at 12 weeks, or sooner in the case of early withdrawal). For patients continuing treatment beyond 12 weeks, the Investigator will review the patient on completion of the planned treatment or at 24 weeks, whichever is sooner.

All anticancer treatment and other prescribed drugs are dispensed by the oncology pharmacists in the respective hospitals, according to local policies. On the designated day, prescribed drugs for patients receiving treatment in the community are dispensed and placed with a copy of the patient prescription sheet in a designated box, ready for collection by the community chemotherapy nurse from the oncology pharmacy at a previously arranged time. The prescription sheet copy is returned to the oncology pharmacy within 48 hours of treatment.

